# Cardiovascular Health Status And Genetic Risk In Survivors of Childhood Neuroblastoma and Nephroblastoma Treated With Doxorubicin: Protocol of the Pharmacogenetic Part of the LESS-Anthra Cross-Sectional Cohort Study

**DOI:** 10.2196/27898

**Published:** 2022-02-17

**Keywords:** cardiotoxicity, anthracyclines, childhood cancer survivors, genetics, polymorphisms, cardiology, cardiac health, cancer, survivors, childhood, children, risk monitoring, genetics, cardiovascular health, pediatrics

## Abstract

**Background:**

In childhood cancer survivors (survival of 5 years or more after diagnosis), cardiac toxicity is the most common nonmalignant cause of death attributed to treatment-related consequences. Identifying patients at risk of developing late cardiac toxicity is therefore crucial to improving treatment outcomes. The use of genetic markers has been proposed, together with clinical risk factors, to predict individual risk of cardiac toxicity from cancer therapies, such as doxorubicin.

**Objective:**

The primary aim of this study is to evaluate the value of multimarker genetic testing for RARG rs2229774, UGT1A6 rs17863783, and SLC28A3 rs7853758 for predicting doxorubicin-induced cardiotoxicity. The secondary aim is to replicate previously described associations of candidate genetic markers with doxorubicin-induced cardiotoxicity. Moreover, we will evaluate the prevalence of cardiovascular dysfunction in childhood cancer survivors after neuroblastoma or nephroblastoma.

**Methods:**

This is the pharmacogenetic substudy of the research project Structural Optimization for Children With Cancer After Anthracycline Therapy (LESS-Anthra). We invited 2158 survivors of childhood neuroblastoma or nephroblastoma treated with doxorubicin according to the trial protocols of SIOP 9/GPOH, SIOP 93-01/GPOH, SIOP 2001/GPOH, NB 90, NB 97, or NB 2004 to participate in this prospective cross-sectional cohort study. The study participants underwent a cardiological examination and were asked to provide a blood or saliva sample for genotyping. The study participants' health statuses and cardiovascular diagnoses were recorded using a questionnaire completed by the cardiologist. Digital echocardiographic data were centrally evaluated to determine the contractile function parameters. Medical data on the tumor diagnosis and treatment protocol were taken from the study documentation. Survivors were screened for variants of several candidate genes by TaqMan genotyping.

**Results:**

This study includes 657 survivors treated with doxorubicin for childhood cancer, the largest German cohort assembled to date to investigate cardiovascular late effects. Data analyses are yet to be completed.

**Conclusions:**

This study will define the genetic risk related to 3 marker genes proposed in a pharmacogenetic guideline for risk assessment. Moreover, the results of this study will show the prevalence of cardiovascular dysfunction in survivors of pediatric neuroblastoma or nephroblastoma who were treated with doxorubicin. The results will help to improve primary treatment and follow-up care, thus reducing cardiovascular late effects in the growing population of childhood cancer survivors.

**Trial Registration:**

German Clinical Trials Register DRKS00015084; https://www.drks.de/drks_web/navigate.do?navigationId=trial.HTML&TRIAL_ID=DRKS00015084

**International Registered Report Identifier (IRRID):**

DERR1-10.2196/27898

## Introduction

Despite the emergence of new so-called targeted therapies, standard cytotoxic chemotherapies remain a cornerstone for treating various cancers. Anthracyclines, such as doxorubicin, daunorubicin, and epirubicin, are still among the most used chemotherapeutic agents. However, cardiotoxicity is a frequent complication with this class of anticancer drugs. In particular, childhood cancer survivors are at risk for cardiovascular complications, with a 15-fold increase in the relative risk of severe congestive heart failure compared to their noncancer siblings [1] and an 8-fold increase in mortality due to cardiovascular disease compared to the overall population [2,3]. Previous studies showed that 4.4%-42% of childhood survivors of acute lymphoblastic leukemia or nephroblastoma had progressive cardiac abnormalities several years after completing doxorubicin therapy [4-6].

Anthracycline-induced cardiomyopathy may develop during treatment or several years after completion of treatment and may include decreased left ventricular ejection fraction and signs and symptoms of congestive heart failure. Many risk factors for anthracycline-induced cardiotoxicity have been identified, most notably higher cumulative anthracycline doses and younger age. However, the optimal strategy for the prevention of anthracycline-induced cardiotoxicity is unclear. Currently, dexrazoxane is the only treatment for anthracycline cardioprotection approved by the United States Food and Drug Administration and European Medicines Agency. However, dexrazoxane is contraindicated in children and adolescents due to a 3-fold higher incidence of secondary malignancies in dexrazoxane-treated children compared with controls.

There is an additive or potentially synergistic increase in the risk of cardiomyopathy or cardiovascular death in anthracycline-treated patients who have received radiotherapy to the mediastinum or concomitant therapy with other known cardiotoxic agents, such as cyclophosphamide or vinca alkaloids [7,8]. Tukenova et al [7] reported that as little as 5 Gy of radiation to the heart increased the relative risk of cardiovascular disease mortality in childhood cancer survivors. New techniques in radiotherapy can increase cardiac protection without losing the efficacy of irradiation [9].

There is extensive interindividual variability in sensitivity to the cardiotoxic effects of anthracyclines. In some patients, cumulative doses of doxorubicin higher than 1000 mg/m^2^ cause no cardiomyopathy, whereas others develop cardiomyopathy at cumulative doses <200 mg/m^2^ [10]. Clinical and experimental studies have shown a considerable genetic contribution [11-13]. The heritability of anthracycline-induced cell toxicity has been estimated to be 35%-60% [11]. Together, the findings suggest that genetic factors play an important role in anthracycline-associated cardiotoxicity.

Candidate gene and genome-wide association studies have identified genetic variants associated with anthracycline-induced cardiotoxicity, including genetic polymorphisms in genes involved in anthracycline transport, metabolism, and anthracycline-induced oxidative stress. Based on their study results, Aminkeng et al [14] concluded that the evidence was strongest and most consistent for an association of *RARG* (retinoic acid receptor gamma) rs2229774, *SLC28A3* (solute carrier family 28 member 3) rs7853758, and *UGT1A6* (UDP glucuronosyltransferase family 1 member A6) rs17863783 variants with anthracycline-induced cardiotoxicity. Testing for these single nucleotide polymorphisms (SNPs) could improve discrimination between individuals at higher and lower risk of anthracycline-induced cardiotoxicity. Aminkeng et al [14] proposed the grading cardiotoxicity risk according to the *RARG* rs2229774, *UGT1A6* rs17863783, and *SLC28A3* rs7853758 genotype, as follows: patients carrying the *RARG* rs2229774 A or *UGT1A6* rs17863783 T risk variants should be considered at high risk of anthracycline-induced cardiotoxicity. The *SLC28A3* rs7853758 A allele was associated with a reduced risk of anthracycline-induced cardiotoxicity. For patients carrying the rs7853758 A protective variant who do not carry *RARG* rs2229774 or *UGT1A6* rs17863783 risk variants, classification into a lower cardiotoxicity risk group should be considered. All other patients should be considered at moderate genetic risk. An initial health economic evaluation of pharmacogenomic testing in patients treated for childhood cancer with anthracyclines suggests that information gained from the pharmacogenomic test could reduce mortality by approximately 17% and reduce costs by about 6% [15].

The primary aim of this study is to evaluate the importance of multimarker genetic testing for *RARG* rs2229774, *UGT1A6* rs17863783, and *SLC28A3* rs7853758 for predicting doxorubicin-induced cardiovascular dysfunction. We focus on these 3 markers because the only pharmacogenetic guideline published to date recommends their testing to stratify the individual cardiotoxic risk of anthracycline therapy. The secondary aim of this study is to determine the association of doxorubicin-induced cardiovascular toxicity with other candidate genes that have been previously described [13,16-19] or will soon be discovered, provided that our sample size has sufficient statistical power. To ensure that the population studied is as homogeneous as possible in terms of diagnoses and the type of anthracycline used, we focus on patients with childhood nephroblastoma or neuroblastoma. Another secondary objective is to investigate the prevalence of cardiovascular dysfunction in a population of children treated with doxorubicin.

## Methods

### Patients

This study is part of the LESS-Anthra cross-sectional cohort study initiated by the “late effects surveillance system” (LESS). As part of this study, former cancer patients were offered a standardized cardiological examination and were surveyed about their quality of life and health status. A goal of LESS-Anthra was to establish a biobank of blood samples to allow the investigation of genetic polymorphisms that may predispose an individual to doxorubicin-induced cardiomyopathy, which is the subject of this study protocol. The study was approved by the Ethics Committee of the University of Lübeck (14-182) and the Ethics Committee of the University of Ulm (239/17). Study participants were identified through LESS, a German multicenter active surveillance consortium studying late effects of cancer treatment in children, in collaboration with the German Childhood Cancer Registry. Patients who had survived childhood cancer for 5 years or more (since diagnosis) were eligible if they (1) were diagnosed with nephroblastoma or neuroblastoma between January 1990 and December 2012, (2) were diagnosed before the age of 18, (3) were assigned to a treatment protocol that included doxorubicin (intention-to-treat), and (4) had participated in one of the nephroblastoma trials SIOP (International Society of Paediatric Oncology) 9/GPOH (German Society for Pediatric Oncology and Hematology), SIOP 93-01/GPOH, or SIOP 2001/GPOH or neuroblastoma trials NB 90, NB 97, or NB 2004. In Germany, almost all patients diagnosed with nephroblastoma or neuroblastoma between 1990 and 2012 who were willing to participate in a trial were included in one of the above-mentioned studies. Patients selected for LESS-Anthra were contacted by the German Childhood Cancer Registry, which has access to current survivor addresses. A total of 2173 patients were identified, contacted by mail, and invited to participate in the study. Those who did not respond received a reminder letter. Patients unwilling to participate in the study had the opportunity to provide us with their reason for nonparticipation via a response form. Patients were included only after they (or their parents or legal guardians, if patients were under 18 years of age) had provided informed consent. For adolescents ≥16 years, their written consent was also required.

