### Collection of Medical Data

The following data were extracted from clinical trial registries: cancer diagnosis, age at diagnosis, sex, tumor location, tumor stage, study name and study arm, chemotherapy, anthracycline doses (doses of doxorubicin, per cycle and cumulatively, as defined in the study protocol for the study arm to which the patient was assigned), other cardiotoxic drugs (ie, drugs with cardiotoxic potential listed in the 2016 ESC position paper [20]), radiotherapy, irradiation field (mediastinal, lung, or left abdominal irradiation is considered a relevant cardiac risk factor [6,21]), irradiation doses of the primary tumor, relapse, and therapy (chemotherapy and irradiation) of recurrent tumor (Textbox 1).

Assessment and variables recorded.
**Cancer diagnosis and cancer treatment-related variables (obtained from study centers of the neuroblastoma trials (NB 90, NB 97, and NB 2004) and the nephroblastoma trials (SIOP 9/GPOH, SIOP 93-01/GPOH, and SIOP 2001/GPOH).**
Cancer diagnosis, tumor location, tumor stageAge at diagnosisSexStudy name and study armChemotherapy including anthracycline doses (per cycle and cumulative)Other cardiotoxic drugs (the drugs listed in the 2016 ESC position paper were considered as potentially cardiotoxic drugs)Additional radiotherapy: irradiation field, irradiation doses of the primary tumor, and the field that included the heart (mediastinal, lung, left abdominal)Length of posttherapy intervalRelapse and therapy (chemotherapy and irradiation) of the recurrent tumorComorbidities

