### Anthracycline Treatment

According to the respective protocol, and dependent on the stage and risk group, the cumulative dose of doxorubicin was 45-240 mg/m^2^ for neuroblastoma patients and 100-400 mg/m^2^ for nephroblastoma patients (Table 5).

**Table 5 table5:** Per protocol cumulative dose of doxorubicin used in the neuroblastoma (NB90, NB97, and NB 2004) and nephroblastoma (SIOP 9/GPOH, SIOP 93-01/GPOH, and SIOP 2001/GPOH) trials.

Study and study arm		Doxorubicin cumulative dose (mg/m^2^)	Single-dose, duration of IV^a^ application

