**NB 2004**			
	Observation group with tumor progression	45 or 180 (depending on further progression after first cycle)	Course N6: 30 mg/m^2^, 4h Course N4: 15 mg/m^2^, 30min
	Medium risk group	180	
	High-risk group	180	

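### Entry and dose follow assignment to doxorubicin, but the cohort, the prevalence and the aims are stated for survivors treated with it

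*Protocol article*

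**What the plan says.** Two places in the protocol article define exposure by assignment:

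- **Methods, Patients, criterion 3:** survivors are eligible if they "were assigned to a treatment protocol that included doxorubicin (intention-to-treat". Receipt of the drug is not a condition.
- **Methods, Collection of Medical Data:** the doxorubicin doses, per cycle and cumulative, are taken "as defined in the study protocol for the study arm to which the patient was assigned". Table 5 under Anthracycline Treatment has the same basis: "Per protocol cumulative dose of doxorubicin used in the neuroblastoma" and nephroblastoma trials.

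Five places name a treated population:

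- **Abstract, Methods:** "We invited 2158 survivors of childhood neuroblastoma or nephroblastoma treated with doxorubicin".
- **Abstract, Results:** "This study includes 657 survivors treated with doxorubicin for childhood cancer".
- **Abstract, Conclusions** and the **closing paragraph of the Discussion:** both promise the prevalence in survivors who were treated with the drug.
- **Introduction, final paragraph:** a secondary objective is to "investigate the prevalence of cardiovascular dysfunction in a population of children treated with doxorubicin".

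The primary aim, in the Introduction and under Statistical Analysis, is prediction of doxorubicin-induced dysfunction. Cumulative doxorubicin dose is a covariate in Models 1 and 3 and in the adjusted single-SNP analyses.

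**The concern.** Patients assigned to a drug and patients treated with it are different populations, and the article defines the first but names the second. Intention-to-treat protects a comparison between randomised arms. Here genotype groups are compared within one cohort in which everyone was assigned to doxorubicin, so the label protects no randomised comparison.

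A patient who was assigned but never exposed cannot have a doxorubicin-induced event and cannot show a gene-drug effect. Adjustment would not help, because the dose covariate would hold the planned dose of the arm instead of zero. If such patients exist and have a lower risk, they pull down the prevalence reported for treated children and weaken the genotype association.

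**Working it through.** **The plan's own figure.** The sample size is not in dispute, but it shows what a diluted odds ratio would mean. Inputs from Estimation of Case Numbers: odds ratio 4.7, allele frequency 6.4% in controls, alpha 5%, power 80%, three controls per case, 10% dropout. Two-sided testing and a continuity correction are my assumptions.

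- Carrier frequency in controls under Hardy-Weinberg: 1 − (1 − 0.064)² = 0.1239.
- Carrier frequency in cases: 4.7 × 0.1239 / (1 − 0.1239 + 4.7 × 0.1239) = 0.3993.
- The two-proportion formula gives 29 cases. 29 / 0.9 = 32.2, so 33 cases and 3 × 33 = 99 controls, as stated.

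**Dilution, base case.** The never-exposed share u is not in the article, so it is varied. Assumed: risk 20% in exposed non-carriers, odds ratio 4.7 among the exposed, and background risk b = 3% in the unexposed regardless of genotype.

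- Exposed carriers: odds 0.25 × 4.7 = 1.175, risk 1.175 / 2.175 = 0.5402.
- Observed risk in each genotype group: (1 − u) × exposed risk + u × b.
- The last column applies the same formula to an assumed overall prevalence of 20% in the exposed.

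| u | Non-carriers | Carriers | Odds ratio | A 20% prevalence reads |
|---|---|---|---|---|
| 0% | 0.2000 | 0.5402 | 4.70 | 20.00% |
| 2% | 0.1966 | 0.5300 | 4.61 | 19.66% |
| 5% | 0.1915 | 0.5147 | 4.48 | 19.15% |
| 10% | 0.1830 | 0.4892 | 4.28 | 18.30% |

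For u = 10%: (0.4892 / 0.5108) / (0.1830 / 0.8170) = 4.28.

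**Other assumptions.** Overall prevalence in the exposed 10% or 25%, background 2% or 5%, RARG carriers 61 of 480 (Table 6: 59 + 2).

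| u | Odds ratio 4.7 reads | 25% reads | 10% reads |
|---|---|---|---|
| 5% | 4.46 to 4.59 | 23.9% to 24.0% | 9.6% to 9.8% |
| 10% | 4.24 to 4.47 | 22.7% to 23.0% | 9.2% to 9.5% |

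Put through the sample-size formula above, an odds ratio of 4.46 needs 31 / 0.9, so 35 cases, and 4.24 needs 33 / 0.9, so 37, against the stated 33.

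**Direction.** Reported prevalence equals exposed prevalence − u × (exposed prevalence − b). It falls only if b is below the exposed prevalence. With b = 20% and exposed prevalence 20%, it does not move. The odds ratio still does: at u = 10%, carriers 0.9 × 0.5402 + 0.02 = 0.5062, non-carriers 0.2000, odds ratio 1.025 / 0.25 = 4.10.

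These figures describe a single-variant odds ratio and a prevalence. The primary analysis judges models by the area under the ROC curve, and no effect on that area has been calculated.

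**The case against.** **The population is openly declared and defensible.** The guideline under evaluation recommends testing all paediatric cancer patients with an indication for doxorubicin or daunorubicin, so the test is used before exposure and an assigned cohort is close to its target. This stands as an argument for presenting the assigned cohort. It does not justify calling that cohort treated.

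**Analysis sets belong to the full protocol or SAP.** That is so, and the absence of a set definition here is not the point. The point is that the article states an entry rule and then names a population the rule does not define.

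**Receipt may not be verifiable.** This stands. The extracted doses are planned ones, and the generic chemotherapy item is not said to record what was given. The fix has to allow for it.

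**Stronger readings to avoid.**

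- A reader might infer that never-exposed patients are in the cohort. Nothing shown says so, and the flowchart in Figure 1, which could list exclusions, is not available.
- A reader might take the NB 2004 observation-group row in Table 5, with a dose of "45 or 180 (depending on further progression after first cycle", as an as-treated rule mixed into an assigned one. The table lists per-protocol doses, and treatment on progression under a trial protocol is still assignment, conditional on an event. Criterion 3 does not say assigned at baseline.
- A reader might conclude that prevalence must be understated. That rests on an assumed low background risk. The endpoint is met by any one of seven criteria, and irradiation and other cardiotoxic drugs are also present, so the background could be higher.

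**Conclusion.** The point holds as a mismatch between the rule that forms the cohort and the population named in its description, prevalence and aims. Any assigned patient who never received doxorubicin would be counted as exposed at the full planned dose, and the article describes no step that would find such a patient. Whether any exist is unknown.

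The likely size is modest. At an assumed 2% to 10% unexposed with 3% background risk, an odds ratio of 4.7 reads about 4.6 to 4.3, and a 20% prevalence loses at most 1.7 percentage points. The published interval for that odds ratio, cited in the article, is 2.7 to 8.3, far wider than the shift. The sample-size calculation is sound as arithmetic. The point is worth settling because it decides to whom the results apply and because the database was not yet closed when the article was written.

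**What to change.** Leave recruitment and the invitation rule as they are, and before database closure:

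1. Check the extracted chemotherapy records or the trial-centre records for receipt of doxorubicin. Where they show that none was given, exclude the patient from the primary genetic analysis and from the prevalence stated for treated survivors.
2. Report how many participants have confirmed, refuted and unconfirmed receipt.
3. Present the full assigned cohort as a sensitivity analysis.
4. If the sources hold only protocol-defined doses and receipt cannot be confirmed, keep the assigned cohort as primary. State the population and conclusions as assigned to doxorubicin-containing treatment in the Abstract (Methods, Results, Conclusions), the last paragraph of the Introduction and the closing paragraph of the Discussion.

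The cost is a record check where records allow it, and a wording change where they do not. The downside is the possible loss of a few patients from the primary set, or a narrower stated conclusion.

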### Study Design

Patients who agreed to participate were asked to see a cardiologist within the next 12 months for a cardiologic follow-up examination, which included an electrocardiogram and transthoracic echocardiography. Patients had the choice of having the examination performed by their supervising cardiologist or a cardiologist recommended by the LESS-Anthra study group. Cardiologists had knowledge of treatment exposure but no knowledge of genotypes. The cardiologists were asked to send original echocardiographic recordings, together with a completed form summarizing the clinical and instrumental examinations results, to the cardiologic evaluation center (Clinic for Pediatric Cardiology at Saarland University Hospital, [name]). The cardiologist also took a blood sample for pharmacogenetic analysis or a saliva sample at the patient's option. Biosamples were sent to the genetics center (Genotyping Laboratory, OZ).

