### Cardiologic Examination

Cardiologists were asked to perform echocardiographic examinations according to the instructions provided. Table 1 shows the minimal digital acquisition protocol for transthoracic echocardiography. The echocardiographic recordings were centrally evaluated by a pediatric cardiologist in a standardized way and blinded for treatment exposure and genetic test results to minimize interinvestigator variability. In rare cases, in which parts of the echocardiography recordings were of insufficient quality, the corresponding data points were treated as missing values.

Additional information, such as clinical examination findings, weight, height, heart rate, blood pressure, and physical performance of the patient, was collected using a questionnaire (Table 1). This questionnaire was completed by the cardiologist and sent to the cardiological evaluation center.

**Table 1 table1:** Minimal digital acquisition protocol for transthoracic echocardiography.

View		Data type
**Long-axis view, M-mode**		Still frame
	At the level of the tip of the posterior mitral valve leaflet (basal myocardial segment)	
**Four-chamber view (2D)**		Loop
	Left atrium and left ventricle, endocardium and myocardium, with mitral valve, left atrium shown with maximum area	
	Right atrium and right ventricle, endocardium and myocardium, with tricuspid valve	
**Short-axis view (2D)**		Loop
	Round section through left ventricle at mitral valve level, right ventricle incised	
**Two-chamber view (2D)**		Loop
	Left ventricle, endocardium and myocardium	
**Three-chamber view (2D)**		Loop
	Left atrium, left ventricle and aorta, endocardium and myocardium, with mitral valve, left atrium shown with maximum area	
**Pulsed-wave or continuous-wave Doppler**		Spectral doppler, still frame
	Mitral valve	
	Tricuspid valve	
	Aortic valve	
	Pulmonary valve	

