### Outcomes

The primary endpoint was cardiac dysfunction, as diagnosed by the cardiologist or revealed by a central assessment of transthoracic echocardiography. Cardiac dysfunction is presumed when at least one of the following criteria is true:

Diagnosis by the cardiologist of heart failure or cardiomyopathy reported in the questionnaire.Left ventricular ejection fraction reduced to <50%.Shortening fraction reduced to <25%.Relative wall thickness reduced to <0.22.Percentage systolic thickening of the interventricular septum and left ventricular (LV) posterior wall reduced to <33%.LV Tei index (myocardial performance index) >0.40.Right atrial volume at end systole/body surface area >30 ml/m^2^.

The secondary endpoint is cardiovascular dysfunction, defined as the composite of arterial hypertension (diagnosed by the cardiologist and reported in the questionnaire or current blood pressure measured during the visit ≥140 mmHg systolic or ≥90 mmHg diastolic), cardiac arrhythmia (diagnosed by the cardiologist and reported in the questionnaire), and cardiac dysfunction (as defined above).

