### Statistical Analysis

The *RARG* rs2229774, *SLC28A3* rs7853758, and *UGT1A6* rs17863783 SNPs were checked for deviations from Hardy-Weinberg equilibrium (HWE). Departure from HWE was defined as *P*-HWE <.01 (after Bonferroni correction of the nominal value of *P* set at .05) and tested by a χ^2^ test of goodness of fit between the observed and expected genotypes.

Our primary aim was to assess the value of multimarker genetic testing for *RARG* rs2229774, *UGT1A6* rs17863783, and *SLC28A3* rs7853758 for predicting doxorubicin-induced cardiovascular dysfunction. To address that aim, we considered the following 3 predictive models. Model 1 includes only clinical risk factors, such as sex, age, irradiation (mediastinal, lung, or left abdominal), the use of other cardiotoxic drugs, length of follow-up, and cumulative dose of doxorubicin. Model 2 includes only genetic profiling. For each individual, the genetic risk will be scored as suggested by the Canadian Pharmacogenomics Network for Drug Safety (CPNDS) Clinical Practice Recommendations Group [14], based on multimarker genetic testing for *RARG* rs2229774, *UGT1A6* rs17863783, and *SLC28A3* rs7853758. Patients carrying the *RARG* rs2229774 A or *UGT1A6* rs17863783 T risk variants will be classified as high genetic risk; patients carrying the *SLC28A3* rs7853758 A protective variant who do not carry *RARG* rs2229774 A or *UGT1A6* rs17863783 T alleles will be classified as low genetic risk; all other patients will be classified as moderate genetic risk (Table 3). Model 3 includes both clinical risk factors and genetic profiling. The independent contribution of each risk factor to the outcomes will be determined using multivariable logistic regression analysis. The predictive accuracy of the model will be assessed by the area under the receiver operating characteristic curve.

**Table 3 table3:** Genetic risk scoring of anthracycline-associated cardiotoxicity as suggested by the Canadian Pharmacogenomics Network for Drug Safety Clinical Practice Recommendations Group [14].

Genetic risk^a^	RARG^b^ rs2229774	UGT1A6^c^ rs17863783	SLC28A3^d^ rs7853758
High	A|G or A|A	Any genotype	Any genotype
High	Any genotype	G|T or T|T	Any genotype
Moderate	G|G	G|G	G|G
Low	G|G	G|G	A|A or A|G

^a^Risk scoring depends on the combined evaluation of three genetic markers, the polymorphisms rs2229774 in *RARG*, rs17863783 in *UGT1A6*, and rs7853758 in *SCL28A3*.

^b^RARG: retinoic acid receptor gamma.

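### A local diagnosis made with knowledge of treatment exposure is enough to make a primary-endpoint case, which could inflate the exposure effects and AUCs of Models 1 and 3 by an unknown amount

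*Protocol article*

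**What the plan says.** On who knew what (protocol article, Study Design): "Cardiologists had knowledge of treatment exposure but no knowledge of genotypes". The same cardiologist reports the diagnoses; Cardiologic Examination says "This questionnaire was completed by the cardiologist and sent to the cardiological evaluation center". The echocardiographic recordings, by contrast, were "centrally evaluated by a pediatric cardiologist in a standardized way and blinded for treatment exposure and genetic test results".

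On the endpoint (Outcomes): "The primary endpoint was cardiac dysfunction, as diagnosed by the cardiologist or revealed by a central assessment of transthoracic echocardiography". The combining rule is "Cardiac dysfunction is presumed when at least one of the following criteria is true", and the first of the seven criteria is "Diagnosis by the cardiologist of heart failure or cardiomyopathy reported in the questionnaire". The other six are echocardiographic thresholds. The secondary endpoint adds arrhythmia, taken only from the cardiologist's diagnosis, and hypertension, taken from that diagnosis or from blood pressure measured at the visit.

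On the models (Statistical Analysis): Model 1 contains sex, age, irradiation, other cardiotoxic drugs, length of follow-up and cumulative doxorubicin dose. Model 2 contains the genetic risk group alone. "Model 3 includes both clinical risk factors and genetic profiling". Accuracy is judged by AUC. Under Collection of Medical Data, the dose is the one laid down for the patient's assigned study arm.

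**The concern.** One route to being a case runs through a person who knows the treatment exposure, and exposure variables are then used to predict who is a case. If a cardiologist is readier to diagnose cardiomyopathy in a patient known to have been heavily treated, part of the association between exposure and outcome comes from the labelling. Because one positive criterion suffices, a normal blinded reading does not correct such a label.

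This would push up the coefficients for dose, irradiation and other cardiotoxic drugs, and with them the AUCs of Models 1 and 3. It can also affect the genetic question. Labels driven by exposure are unrelated to genotype, so they dilute the genetic odds ratios while strengthening the clinical model against which the score is naturally compared. The secondary endpoint shares the weakness through locally diagnosed arrhythmia and hypertension.

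**Working it through.** **Passages side by side.** (1) The local cardiologist knows the exposure and not the genotype. (2) That cardiologist's questionnaire diagnosis is sufficient by itself for the primary endpoint, and no central confirmation of it is described. (3) Blinding to exposure covers only the central reading, which supplies the other six criteria. (4) Exposure variables are predictors in Models 1 and 3. The route from exposure knowledge to case status is therefore open, but only for patients who meet the first criterion and none of the other six.

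**Plan's own figure.** The article gives no figure on this point. Its planned 33 cases and 99 controls concern the RARG replication and are unaffected.

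**Illustration 1: exposure only (all values assumed).** Exposure is split 50/50 with no true effect. True risk is 8% in both halves, and a fraction f of the remaining patients is labelled by local diagnosis alone. Observed prevalence = 1 − (1 − 0.08)(1 − f). AUC = 0.5 + 0.5 × [P(high | case) − P(high | non-case)].

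- f = 4% (high) and 1% (low): prevalence 1 − 0.92 × 0.96 = 11.7% and 1 − 0.92 × 0.99 = 8.9%. Odds ratio = (0.1168/0.8832)/(0.0892/0.9108) = 1.35. AUC = 0.5 + 0.5 × (0.567 − 0.492) = 0.537. Label-only share of cases = 0.92 × 0.05/(0.1168 + 0.0892) = 22%.
- f = 2% and 0.5%: prevalence 9.8% and 8.5%, odds ratio 1.18, AUC 0.521, label-only share 13%.

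A second simulation assumed a continuous exposure score, 10–20% prevalence, 5–30% of cases resting on local diagnosis alone, and a diagnostic odds ratio of 2–3 per SD. The exposure AUC moved from 0.50 to 0.51–0.61 with no true effect, and from 0.61 to 0.62–0.69 with a true odds ratio of 1.5 per SD. With no label-only cases it did not move.

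**Illustration 2: the gain of Model 3 over Model 1.** Genetic group shares come from Table 7 (72, 301 and 107 of 480). Exposure is taken as binary, 50/50 and independent of genotype. Cell odds = base odds × genetic OR × exposure OR, giving true risk p. Observed risk q = 1 − (1 − p)(1 − f). AUC = P(case scores higher) + 0.5 × P(tie), scoring each group by its risk.

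First row in full: true risks for high, moderate and low genetic risk are 11.5%, 8.0% and 5.5%. The genetic AUC is then 0.560 against 0.500 for exposure, a gain of 0.060. After labelling, observed risks (high/low exposure) are 15.1/12.4%, 11.7/8.9% and 9.3/6.5%. Model 3's AUC is 0.565 and Model 1's 0.537, a gain of 0.028.

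| True prevalence | Exposure OR | Genetic OR (high/low) | Labels f | Model 1 AUC | Gain |
|---|---|---|---|---|---|
| 8% (moderate group) | 1 | 1.5/0.67 | 4%/1% | 0.500 → 0.537 | 0.060 → 0.028 |
| 8% (moderate group) | 1 | 2/0.5 | 4%/1% | 0.500 → 0.537 | 0.102 → 0.060 |
| 8% (moderate group) | 1 | 1.25/0.8 | 4%/1% | 0.500 → 0.538 | 0.033 → 0.013 |
| 20% (moderate group) | 1 | 1.5/0.67 | 4%/1% | 0.500 → 0.518 | 0.060 → 0.045 |
| 8% (overall) | 2.5 | 2/0.5 | 4%/1% | 0.607 → 0.621 | 0.054 → 0.039 |
| 8% (overall) | 2.5 | 2/0.5 | 2%/0.5% | 0.607 → 0.615 | 0.054 → 0.046 |
| 20% (overall) | 2.5 | 2/0.5 | 4%/1% | 0.608 → 0.616 | 0.053 → 0.047 |
| 20% (overall) | 2.5 | 2/0.5 | 2%/0.5% | 0.608 → 0.612 | 0.053 → 0.050 |

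The loss is largest when exposure has no true effect and small when it has a real one.

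**The case against.** The article says only that treatment exposure was known. Every eligible patient was assigned to a doxorubicin protocol, so knowing that a patient received the drug separates nobody. Differential suspicion needs knowledge of dose, irradiation field or other drugs, and the modelled dose is the protocol-assigned one, which the cardiologist may not have known. Six of the seven criteria are read blinded. The local diagnosis is also structured (heart failure type and NYHA stage, cardiomyopathy type) and follows ECG and echocardiography. The Introduction names higher cumulative dose as a leading risk factor, so the scenarios without a true exposure effect are the extreme ones. Sensitivity analyses are often left to an analysis plan, which is not shown here.

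Most of this stands as a limit on size. It does not close the route: the endpoint rule, the unblinded source and the predictors are all fixed in the article. The Discussion also acknowledges that no echocardiographic definition of this toxicity is generally agreed, which leaves room for judgement in a diagnosis. And the plan itself shielded the central reader from exposure, a safeguard that the first criterion bypasses.

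A reader might infer three stronger things that the documents do not support:

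- That dose and irradiation are demonstrably built into the outcome. No count of cases resting on local diagnosis alone is given, and nothing shows that diagnoses were swayed.
- That an AUC inflation of 0.02–0.04 can be set directly against the genetic gain. Inflation enters Model 3 as well as Model 1, so the change in the gain has to be computed, as above. The article also does not state that genetics will be judged by Model 3 minus Model 1; that is the natural use of the three models, but an inference.
- That the genotype classification is contaminated. The cardiologists did not know genotypes.

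**Conclusion.** The concern holds as a risk created by the stated endpoint rule, with a size that the documents do not allow anyone to compute. Local diagnoses made with knowledge of exposure could inflate the coefficients for dose, irradiation and other cardiotoxic drugs and the AUCs of Models 1 and 3, and could make the genetic score look less useful than it is. Two unknowns decide whether it matters: how many patients are cases by the first criterion alone (zero means no bias), and how far the cardiologist's knowledge tracks the modelled exposure.

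In the scenarios of Illustration 2, the loss of genetic gain ranges from negligible (0.003, with a real exposure effect, 20% prevalence and few label-only cases) to about half or more of the gain (0.060 to 0.028, with no exposure effect and 22% of cases label-only). The prevalence, odds ratios and label rates are assumptions; only the genetic group shares come from the article. This justifies a sensitivity analysis and a cautious conclusion, and does not justify replacing the endpoint.

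**What to change.** - Keep the composite as the primary endpoint.
- Report how many patients are cases by the local diagnosis alone, by level of dose, irradiation and other cardiotoxic drugs. If there are none, the matter is closed for the primary endpoint.
- Before database closure, pre-specify a sensitivity analysis that reruns Models 1–3 with cardiac dysfunction defined by the six centrally read criteria only.
- If the exposure effects or the Model 3 versus Model 1 comparison differ materially, report both versions and qualify the statements on clinical factors and incremental value. Do not default to the central-only version: a difference does not by itself show which version is wrong.
- State that arrhythmia, and hypertension where it rests on the local diagnosis, carry the same limitation in the secondary endpoint. The article describes no central reading for either.

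The cost is one extra run of three models and one table, on data already collected. The timing is right: the article describes the database as still open and the outcome definitions as still adjustable. The downside is that the sensitivity version has fewer cases and omits patients with diagnosed disease whose current echocardiogram is normal. If those patients cluster among the heavily exposed, it would understate the exposure effects.
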